The recent results of the MANGO study, carried out in Burkina-Faso, showed that the reduction in the dose of RUTF after two weeks of treatment of children suffering from SAM, defined by PT  $< -3$ zscore and / or MUAC  $< 115$  mm and no edema at all, reduced neither weight gain (3.4 g / kg / day; 95% CI -0.4 to 0.4;  $p = 0.92$ ) nor rate of girth gain brachialis (BP), does not affect healing or prolong the duration of treatment (with a median of 56 days; interquartile range [IQR] 35-91) although a small negative effect (0.2 mm / week; 95% CI: 0.04 to 0.4;  $p = 0.015$ ) was observed on linear growth especially for the youngest subjects (24). This study was able to show that children with a reduced dose of RUTF had the same body composition as those who received the standard dose, and came out cured with a fat-free mass almost at the same level as that of healthy children in the community.(25). In terms of energy, reducing the dose

of RUTF leads to a reduction in the daily intake but nevertheless makes it possible to cover the daily energy needs of children treated for uncomplicated SAM.(26).

The MANGO study demonstrates that a reduced dose of RUTF would be as effective as the standard dose in the management of uncomplicated SAM under ideal conditions. It is in this context that we propose to carry out the EfRAMAS project to confirm this in a situation of food insecurity and without additional staff to collect data on children who suffer from SAM in the DRC.

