#### **b. Specific objectives**

##### **Primary objective**

To assess the effectiveness of a reduced dose of RUTF in the management of SAM in children aged 6 to 59 months on the rate of weight gain (g / kg / d) from admission to discharge .

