### 2.1.2. Participants

#### a. Inclusion criteria

To participate in this study, individuals must meet the following criteria:

- Be between 6 and 59 months old;

- To be MAS: PT <-3 Z-score and / or PB <115mm and / or bilateral edema (+, ++);
- Not having any medical complications;
- Have a good result on the appetite test;
- Live in the selected health zone;
- Consent to participate in the study (informed consent);
- Not have other siblings already admitted to the study. When there are several participants in the same siblings, only the first will be included in the EfRAMAS project. The others will be covered according to the national program but will not be part of the study.

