#### ***During the weekly consultation:***

- Increase / development of nutritional edema;
- If the appetite test fails (poor appetite);
- Appearance of signs of medical complications;
- Appearance of re-nutrition diarrhea leading to weight loss;
- Presence of one of the "treatment failure" criteria:
  - Weight loss for 2 consecutive weeks;
  - Weight loss of more than 5% of body weight at any one visit;
  - Weight stagnant for 3 consecutive weighings.

All the children admitted to the study and who will be transferred to UNTI, will then return to research in their respective groups. On their return, the children in the reduced dose arm will resume the planned dose the week they were transferred, so they do not restart the treatment from zero but continue it.

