##### b. Additional results

The additional results expected in this study, in the two groups (control and intervention), are:

- **The duration of the edema melting:** calculated in number of days, this indicator corresponds to the time taken for the lower limbs of SAM children to return to their normal volume. The expected result is the onset of melting of the edemas within the first 14 days after admission and their complete disappearance after 21 days of treatment.
- **The length of stay:** calculated in number of days, this indicator corresponds to the time elapsed between admission and discharge ( $PB \geq 12.5\text{cm}$  and / or  $PT \geq -3$  Z score and / or edema melt). The maximum length of stay is 12 weeks or 3 months(12).
- **The cure rate:** A child will be considered cured if he meets the cure criteria according to his admission category: A  $PT \text{ index} \geq -1.5$  or  $PB \geq 125 \text{ mm}$  during two consecutive visits and no edema during two visits (2 consecutive weeks).
- **The dropout rate:** it is the proportion of children confirmed alive who missed two successive visits. The abandonment is confirmed once after the visit of the RECO which confirms that the child is alive despite his 2 absences during the weekly visits. Children who have abandoned will be followed up to 3 months after the abandonment. For children who can be found, offer the caregivers a small snack at the single appointment 3 months after abandonment to take the anthropometric measurements.
- **Death rate :** the proportion of children randomized to the study who died during the intervention at any time.
- **Cost savings** (average cost saved and cost saved per child treated): this involves comparing the cost of treatment for children in care and declared cured in the two groups. We will use a societal perspective including the direct costs of drugs and RUTF

(purchase, transport, transport and storage) to assess the cost for each child, the HR costs involved in the care, the non-medical costs (food and transport. beneficiaries), indirect costs (loss of productivity).

- The growth velocity of the anthropometric variables and indices: it will be a question of evaluating the prevalence of stunting, underweight of the children included in the study in the two groups at the end of the treatment.

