## Annex 8: List of variables according to specific objectives

| Specific objectives                                                                                                                                                                                                                                                                                                                 | Variables                                   | Definition                                                                                                                 | Values                                                                                | Ladder   |
|-------------------------------------------------------------------------------------------------------------------------------------------------------------------------------------------------------------------------------------------------------------------------------------------------------------------------------------|---------------------------------------------|----------------------------------------------------------------------------------------------------------------------------|---------------------------------------------------------------------------------------|----------|
| Primary objective                                                                                                                                                                                                                                                                                                            |                                             |                                                                                                                            |                                                                                       |          |
| Evaluate, on an outpatient basis, without additional staff to collect data and in a food insecure situation, the effectiveness of a reduced dose of RUTF in the management of SAM with edema in children aged 6 to 59 months over the rate of weight gain (g / kg / d) of children aged 6 to 59 months from admission to discharge. | PB                                          | Measurement of the Circumference of the arm halfway between the acromion between the olecranon in cm                       | Normal: $\geq 12.5$ cm
MAS: $< 11.5$ cm
MAM: $\geq 11.5$ and $< 12.5$ cm        | interval |

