|                                                                                                                                                                                                                                                                                                                                     | Presence of edema                           | Increased volumes of the lower limbs taking the bucket                                                                     | Absent: normal volume
+ or ++                                                      | nominal  |
|                                                                                                                                                                                                                                                                                                                                     | Rate of weight gain in children             | Ratio of the difference in weight between discharge and admission / initial weight / duration of treatment (g / kg / d)    | number                                                                                | interval |
|                                                                                                                                                                                                                                                                                                                                     | SAM proportion without complications.       | Ratio of all uncomplicated SAM children to the total of AD children received during recruitment                            | %                                                                                     | interval |
|                                                                                                                                                                                                                                                                                                                                     | Sex                                         | Child gender                                                                                                               | Male
Feminine                                                                      | nominal  |

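### Weight-gain velocity is taken from the admission weight even in children admitted with oedema, so it mixes fluid loss with tissue gain and makes the 5 and 4.5 g/kg/day readings unreliable

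*Protocol*

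**What the plan says.** The primary objective (section 1.2) is the effect of the reduced dose "on the rate of weight gain (g / kg / d) from admission to discharge". Annex 8 gives the only formula: "Ratio of the difference in weight between discharge and admission / initial weight / duration of treatment (g / kg / d". It makes no exception for oedema, and no other section supplies a different start weight.

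Oedematous children are clearly in the trial. The inclusion criteria (2.1.2 a) admit "PB <115mm and / or bilateral edema" of grade + or ++, and Annex 8 words the primary objective as "the effectiveness of a reduced dose of RUTF in the management of SAM with edema in children aged 6 to 59 months". Section 2.1.4 b expects "onset of melting of the edemas within the first 14 days after admission" and complete disappearance after 21 days. Cure requires absence of oedema for 14 days (1.3) or at two visits (2.1.4 b). During treatment, "Increase / development of nutritional edema" is a criterion for transfer (2.1.3 a).

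Section 2.1.4 a names 5 g/kg/day as acceptable and says the intervention group should not fall below 4.5. Section 2.3.3 plans linear regression in adjusted and unadjusted models and names no covariates. The earlier trial whose result is to be confirmed enrolled children with "and no edema at all" (1.1).

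**The concern.** The admission weight of an oedematous child includes fluid that the protocol expects the child to lose before discharge. That loss is subtracted from the tissue gain in the numerator, and the fluid inflates the denominator. The recorded velocity is then no longer a measure of growth in these children.

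Three things are at stake. First, the absolute reading: an arm could approach or miss 4.5 g/kg/day because of its case mix and not because of the dose. Second, precision: mixing children with and without fluid loss adds variance. Third, the arm difference: the doses diverge from week 3 while clearance is expected to run to about day 21. If the reduced dose slowed clearance, its children would carry more fluid at later weighings and look better.

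**Working it through.** **The plan's own figure.** Section 2.1.6 uses SD 2.6, margin 0.5, true difference 0, one-sided 5% and 80% power. With unrounded normal quantiles, n = (1.645 + 0.842)² × 2 × 2.6² / 0.5² gives 335 per arm, as stated. The rounded 1.64 and 0.84 give 332.6. With 1,000 children and 20% dropout, 400 per arm are evaluable.

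**Inputs for the check.** Durations D come from the protocol: 42 days (the average stay in the Burma programme, 1.1), 56 days (the median in the earlier trial, 1.1) and 84 days (the 12-week maximum). The fluid share f of admission weight and the oedematous share p are not in the documents. They are assumptions, shown as ranges.

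**One child.** Let tissue gain be 5 g/kg/day on dry weight, with all fluid lost by discharge. Then recorded velocity = 5 × (1 − f) − 1000 × f / D.

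| f | D = 42 | D = 56 |
|---|---|---|
| 3% | 4.85 − 0.71 = 4.14 | 4.85 − 0.54 = 4.31 |
| 5% | 4.75 − 1.19 = 3.56 | 4.75 − 0.89 = 3.86 |
| 8% | 4.60 − 1.90 = 2.70 | 4.60 − 1.43 = 3.17 |

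Every value is below 4.5. If the fluid is fully retained, the second term vanishes. At 5% the child scores 4.75, which is still below the true 5.

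**Arm mean.** The fluid-loss term lowers the mean by p × 1000 × f / D. With p = 30%, f = 5% and D = 56 this is 0.30 × 0.89 = 0.27. Including the inflated denominator it is 0.30 × (5 − 3.86) = 0.34. Over p = 10–50%, f = 3–10% and D = 42–84, the fluid-loss term runs from 0.04 to 1.19. An arm with a true mean of 5 drops below 4.5 once p exceeds 0.5 divided by the shortfall per child:

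- f = 5%, D = 56: 0.5/1.14 = 44%
- f = 8%, D = 42: 0.5/2.30 = 22%
- f = 3%, D = 56: 0.5/0.69 = 73%

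**Precision.** If the fluid variation adds to the planned SD, SD = √(2.6² + p(1 − p) × shift²), where shift = 1000 × f / D. The central case gives √(6.76 + 0.21 × 0.89²) = 2.63 and n = 343 per arm. Over the full ranges the SD is 2.60–2.86, n is 335–405, and power with 400 per arm is 80–86%.

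**Arm difference.** Two routes can bias it.

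- *Fluid still present at exit.* If an extra 5% of one arm's children leave with 5% fluid, the difference shifts by 0.05 × 50/56 = 0.045 g/kg/day. An extra 10% with 10% fluid shifts it by 0.10 × 100/56 = 0.18.
- *Longer stay.* With 5% fluid the penalty is 50/42 = 1.19 at 42 days and 50/56 = 0.89 at 56 days. At equal tissue velocity, an arm staying two weeks longer gains 0.30 among its oedematous children, or 0.06 overall if p = 20%.

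**The case against.** The strongest reply is that the trial's claim rests on a randomised difference, not on a level. Allocation is balanced within blocks at each UNTA (2.2.1) and both arms receive the same dose in weeks 1–2 (2.1.3), when oedema should begin to melt. Most fluid loss should therefore fall equally on both arms. This stands, and it is why the between-arm effect is modest.

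A longer stay also need not hide a real loss. If the same 210 g/kg of tissue takes 56 days instead of 42, true velocity falls from 5.00 to 3.75. At 5% fluid the formula records (199.5 − 50)/42 = 3.56 and (199.5 − 50)/56 = 2.67. The true gap of 1.25 shrinks to 0.89, which still exceeds the margin and has the right sign. The protocol in any case hypothesises equal stay.

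Slow clearance would also be visible, because duration of oedema melting is a separate outcome. Annex 8 lists presence of oedema among the primary-objective variables, and the covariate list may sit in an SAP that is not shown. All fair, but the formula itself is fixed in the protocol, and neither a separate outcome nor a covariate restores the absolute level. The planning mean of 5 might already allow for fluid loss, but section 2.1.6 does not say so.

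A reader might infer that retained oedema is scored as weight gain. It is not: the fluid is in both weights and cancels in the numerator. Such a child only scores higher than one who cleared the fluid. A reader might also infer that new oedema inflates the result generally. It would count as gain, but it triggers transfer, and both cure definitions require its absence. The per-protocol set of cured children is therefore protected, and only non-cured exits in the intention-to-treat set are exposed.

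**Conclusion.** The concern holds in a limited form. In children admitted with oedema, the primary velocity mixes fluid loss with tissue gain. At an assumed 3–8% fluid share, a true 5 g/kg/day is recorded at about 2.7–4.1 over 42 days or 3.2–4.3 over 56 days. Both arm means are lowered by an amount that cannot be fixed without the oedematous share, so the 5 and 4.5 figures are unreliable for the mixed population.

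The cost in power is small. The possible bias in the arm difference is about 0.05–0.2 g/kg/day in the scenarios tried. It points towards non-inferiority if the reduced dose slows clearance after week 2, and it is below the 0.5 margin.

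It is tempting to say that the error exceeds the margin and invalidates the primary outcome. That does not follow. The error is a shift in level within a child, whereas the margin applies to the difference between arms, where most of the shift should cancel.

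**What to change.** Change the wording in 2.1.4 a, 2.3.3 and Annex 8 before data are seen:

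1. Adjust the primary model for oedema at admission (yes/no). This removes the variance between the two groups of children and corrects chance imbalance. It does not correct the level.
2. Prespecify that the primary result is also reported separately for children without and with oedema at admission. State that the 5 and 4.5 g/kg/day figures are not to be read against admission-weight velocity in oedematous children.
3. Add a prespecified sensitivity analysis in which velocity for oedematous children runs from the first oedema-free weekly weight and its date. Give a rule for children who never become oedema-free or have no later weight, for example keeping the admission-weight value, so that no randomised child is dropped.

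Item 3 should not replace the primary definition. Its start weight is post-randomisation, can fall after the doses diverge and shortens the window. Without a fallback rule it would also be undefined for children whose oedema persists or clears only at the last visit.

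The cost is a little more analysis. Weight and oedema are already recorded weekly (Chart 5), so no new data are needed.

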### **b. Modification or interruption of the intervention**

During the implementation of this study, the intervention will be interrupted for each participant who presents (12):

- Withdrawal of informed consent;
- Discontinuation of treatment;
- Lost view ;
- Failure to process.

Chart 3 : Criteria for leaving the study outside of the cure

| Criteria                                        | Definition                                                                                                                                                       |
|-------------------------------------------------|------------------------------------------------------------------------------------------------------------------------------------------------------------------|
| Abandonment-confirmed                           | Patient absent for two consecutive weeks (declared abandonment in the third) sought by the RECOs and confirmed as having abandoned                               |
| Unconfirmed abandonment                         | Patient absent for two consecutive weeks (declared abandonment in the third) but his actual method of discharge (abandonment or death) not having been confirmed |
| Death                                           | Participant whose death has been certified by a nursing staff                                                                                                    |
| Lost view                                       | Change of address, followed in another CS outside the study area                                                                                                 |
| Treatment failure                               | Referred to UNTI following the appearance of danger signs (temporary discharge *)                                                                                |
| Withdrawal of consent                           | Any time after randomization                                                                                                                                     |
| Non-response to treatment (even if very rarely) | Children who do not recover after 12 weeks of treatment                                                                                                          |

*\*AT their return the children of the arm with reduced dose will resume with the dose planned for the week in which they were transferred, so they do not restart the treatment from zero but continue it.*

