- The accompanying person should wash their child's hands and face with soap before giving RUTF;
- Specify to the accompanying person the amount of RUTF that their child must eat per day;
- The treatment must be respected: for a good recovery, the child must be consulted every week for a minimum period of 1 month and a half;
- The accompanying person must return the empty sachets of RUTF and the sachets not consumed to the UNTA
- caregivers and family members should not consume RUTF instead of the child, even for reasons of breastfeeding or feeding other children.

Chart 6 : Appraisal of the appetite test based on the proportion of dough consumed

| Body weight
(kg) | RUTF - paste in sachet
(Proportion of a whole bag 92g) |            |       |
|---------------------|-----------------------------------------------------------|------------|-------|
|                     | Weak                                                      | Average    | Good  |
| <4                  | <1/8                                                      | 1/8 - 1/4  | > 1/4 |
| 4 to 6.9            | <1/4                                                      | 1/4 - 1/3  | > 1/3 |
| 7 to 9.9            | <1/3                                                      | 1/3 - 1/2  | > 1/2 |
| 10 to 14.9          | <1/2                                                      | 1/2 - 3/4  | > 3/4 |
| 15 to 29            | <3/4                                                      | 04/03 to 1 | > 1   |
| > 30                | <1                                                        | > 1        |       |

To have good results in the appetite test, the following measures must be observed:

- Wash your child's hands and face and hands before giving RUTF;
- Obtain a cup of drinking water;
- Find a comfortable place;
- Do not force the child to eat;
- Check if the child has eaten in the last 30 minutes.

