## **f. Organization of the collection**

### ***At UNTA level***

On admission, if a patient meets the study inclusion criteria, the receiving provider explains how the study is going and requests informed consent to include them in the study. If consent is obtained, the nurse assigns an ID to the child that matches the randomization ID. The randomization group is not mentioned. Information on socio-demographic characteristics is collected by IT.

The provider responsible for medically examining the child and taking the anthropometric measurements examines and provides information on the measurements. Anthropometric measurements will be taken according to the PCIMA protocol once a week when the child visits the center until the cured discharge or up to 12 weeks maximum.

- PB will be measured using a PB tape on the left arm halfway between the acromion and the olecranon;
- The weight using a SECA scale depending on whether or not the child can stand up;
- The height will be measured using a wooden measuring board in the supine or upright position depending on whether the child is <24 months or ≥24 months (or ≥ 87 cm) respectively;
- Edemas will be assessed according to their importance (0; + if limited to the feet; and ++ if limited to the legs).

The medical treatment is given to the child according to what is defined in the PCIMA protocol.

Finally, the child receives the amount of RUTF planned for the week as well as health education. It is the same provider in charge of the admission who will ensure the distribution of RUTF and will know who receives the reduced dose according to the IDs of the children. This provider will not follow up on children to keep blind. Each participant receives the quantity of RUTF described in Table 1 (presented above).

All the information on the identifier, the socio-demographic characteristics and the anthropometric measurements are noted in the individual follow-up sheet of the corresponding participant.

**Assessment of psychomotor development:** Depending on the sampling interval, the evaluation of psychomotor development will be carried out on 40% of the sample size, by means of the ASQ 3 score and will include two parts: the execution of the tasks by the child and the filling

of the questionnaire by the guides. For each child, the performance will only last between 10 to 15 minutes. The results of the assessment of psychomotor development are listed in the corresponding item.

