| Evaluate the duration of treatment for each participant in the two groups                    | Duration of the treatment                    | Time between admission and discharge (PB≥12.5cm or PT ≥-3 Z score or edema melt)                                                                                                         | number of days           | interval |
| Assess dropout, cure, treatment failure and mortality rates                                  | Dropout rate in each arm                     | Number of children who have abandoned treatment and who no longer come to the center even after 3 home visits / total of children followed in each arm                                   | percentage               | interval |
|                                                                                              | Recovery rate                                | Percentage of children having reached the discharge after 3 months of treatment                                                                                                          | percentage               | interval |
|                                                                                              | Proportion Transfer to hospital in each arm  | Number of children being transferred to hospital during treatment (3 months) following a medical complication or if stagnation or loss of appetite / total children followed in each arm | percentage               | interval |
|                                                                                              | Proportion of Deaths in each arm             | Number of children who died during the stay at UNTA or during transfer to UNTI / total child followed in each arm                                                                        | percentage               | interval |
| Evaluate the cost and savings made with a reduced dose of RUTF compared to the standard dose | % savings in SAM treatment with reduced dose | Difference in cost between treatment with standard dose and treatment with reduced dose, expressed in%                                                                                   | percentage               | interval |

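### Length of stay and duration of treatment describe discharge as PT ≥ −3, which contradicts the cure rule and leaves the divisor of weight-gain velocity ambiguous

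*Protocol*

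**What the plan says.** Two definitions in the protocol describe the end of treatment by a low threshold.

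- Annex 8, row on duration of treatment: "Time between admission and discharge (PB≥12.5cm or PT ≥-3 Z score or edema melt".
- Section 2.1.4 b, length of stay: "this indicator corresponds to the time elapsed between admission and discharge". The parenthesis that follows lists the same PB, PT and edema criteria, joined by and/or.

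Other parts describe a different end point.

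- Section 2.1.4 b, cure rate: by admission category, PT ≥ −1.5 or PB ≥ 125 mm "during two consecutive visits and no edema during two visits (2 consecutive weeks").
- Section 1.3: recovery, judged according to the admission criteria, needs PT ≥ −1.5 at two consecutive weighings, PB ≥ 125 mm and 14 days free of edema.
- Section 2.3.1 f: measurements are taken "once a week when the child visits the center until the cured discharge or up to 12 weeks maximum".
- Section 2.1.3 b, Chart 3: non-response means "Children who do not recover after 12 weeks of treatment".

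The primary outcome is linked to the first pair. Annex 8 defines the rate of weight gain as "Ratio of the difference in weight between discharge and admission / initial weight / duration of treatment (g / kg / d"). The primary objective in section 1.2 runs from admission to discharge.

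**The concern.** The PT threshold of −3 is the entry criterion turned round. Section 2.1.2 a admits on "To be MAS: PT <-3 Z-score and / or PB <115mm and / or bilateral edema", and the PT row of Annex 8 classes −3 to below −2 as moderate acute malnutrition. A child at PT −2.9 has left the severe range but is not cured under any rule in the protocol.

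Length of stay is a named secondary objective with its own hypothesis of equality between arms. An analyst who programs it from either definition would measure the time to leave the severe PT range, or something shorter, and not the stay.

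The term duration of treatment is also the divisor of the primary outcome, and its own Annex 8 row is the one with the −3 threshold. Two analysts could therefore derive different velocities from the same data, each with support in the text.

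**Working it through.** The plan gives no figure for this point. Its sample size does not depend on it and reproduces: (1.64 + 0.84)² × 2 × 2.6² / 0.5² = 332.6 with the rounded Z values, and 335 per group with unrounded ones, as stated.

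**Step 1: the definitions side by side**

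| Item | PT | PB | Edema | Confirmation | Combination |
|---|---|---|---|---|---|
| Length of stay (2.1.4 b) | ≥ −3 | ≥ 12.5 cm | melted | none stated | and/or |
| Duration of treatment (Annex 8) | ≥ −3 | ≥ 12.5 cm | melted | none stated | or |
| Cure rate (2.1.4 b) | ≥ −1.5 | ≥ 125 mm | absent | two consecutive visits; two consecutive weeks for edema | by admission category |
| Recovery (1.3) | ≥ −1.5 | ≥ 125 mm | absent 14 days | two consecutive weighings for PT | according to admission criteria |

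The PB value agrees throughout. The PT value does not. Because −3 stands in two separate places, it is not a slip in reading one line of the PDF.

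**Step 2: a child who enters with PT at or above −3**

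Entry on PB or edema alone is allowed. Take a child with PB below 115 mm and PT −2.5. One of the alternatives joined by "or" is already met at admission, so the duration is 0 days and a velocity divided by it is undefined. Yet section 2.1.3 e tells caregivers that "the child must be consulted every week for a minimum period of 1 month and a half".

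**Step 3: a child who enters on PT (illustration)**

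Assumptions not in the documents: one z-score equals a share s of median weight, with s from 0.07 to 0.09, and height stays constant. From section 2.1.6: gain of 5 g/kg/day, taken here relative to admission weight. With admission at z₀, the days from PT −3 to PT −1.5 are

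(1000 / 5) × 1.5s / (1 + s·z₀).

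For z₀ = −3.5:
- s = 0.07: 200 × 0.105 / 0.755 = 27.8 days
- s = 0.08: 200 × 0.120 / 0.720 = 33.3 days
- s = 0.09: 200 × 0.135 / 0.685 = 39.4 days

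For z₀ between −3.2 and −4.0 the range is 27 to 42 days. This is the gap for one child between two thresholds. It is not a difference between arms.

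**Step 4: the primary outcome**

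Velocity = (exit weight − admission weight) / admission weight / T. Three readings of T are possible.

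- T and weight both at actual discharge: this is what sections 1.2 and 2.3.1 f suggest, and the outcome is unaffected.
- T and weight both at the −3 threshold: a larger share of the interval falls in the first two weeks, when both arms get the same dose, so any difference tends to shrink.
- Weight at discharge but T at the threshold: the divisor is too short, so velocities rise and, with equal T in both arms, any difference grows.

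The last two readings pull in opposite directions, so the text fixes neither a size nor a sign.

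**The case against.** The strongest reply is that both definitions measure time to discharge, and the parenthesis only describes that event badly. Actual discharge is governed by section 1.3, the cure definition, the follow-up rule in section 2.3.1 f and the exits in Chart 3. A child just admitted has not been discharged, so day 0 arises only if the parenthesis overrides the word discharge. This stands as a limit: the harm is conditional on deriving the variable from the listed criteria. It does not remove the error, because those criteria are the only operational content the two definitions give.

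Several stronger readings are tempting and are not supported.

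- **Children would be sent home at PT −3.** No section instructs this; follow-up runs to cure or 12 weeks.
- **The definitions accept a single visit.** They state no number of visits. That none is required is an inference from silence.
- **The primary analysis is biased towards non-inferiority.** Any figure would need assumed stop times and an assumed deficit, and the readings in Step 4 disagree in direction.
- **The cure rate is wrong.** Section 2.1.4 b defines it explicitly. The recovery-rate row of Annex 8 does rest on the word discharge, so it gains from the same clarification.
- **Section 1.3 contradicts the cure rule.** Its conjunctions are loose, but it too applies by admission criteria, and its 14 edema-free days can be the same period as two consecutive weeks.

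**Conclusion.** The point holds as a contradiction in two outcome definitions, and it should be fixed. Length of stay and duration of treatment describe discharge by a PT threshold that conflicts with the cure rule and with follow-up to cured discharge.

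If the parenthesis is applied as written, length of stay is wrong for PT admissions (by roughly four to six weeks under the assumptions in Step 3) and can be 0 days for PB or edema admissions. If the actual discharge date is used, there is no numerical harm.

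For the primary outcome the finding is one of ambiguity only: the divisor has two possible meanings, and the more natural one leaves the result intact. Treatment, randomisation, margin and sample size are not in question.

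**What to change.** 1. In section 2.1.4 b (length of stay) and Annex 8 (duration of the treatment), delete the parenthesis and refer to the protocol's cure rule.
2. Add one sentence there and in the Annex 8 row on rate of weight gain: length of stay, duration of treatment and velocity all use the date and weight at actual exit, whether cured or another exit, at most 12 weeks after admission.
3. In section 1.3, only clarify that the criteria apply by admission category, as in the cure definition. Leave the rule itself alone: rewriting its edema-free period could change when children are discharged, and the national protocol it follows is not available to check.

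The cost is a text amendment to a few sentences. Treatment, visit schedule, data collection and sample size do not change. It should be made before the outcome variables are derived, so that the divisor of the primary outcome is not chosen with data in hand.
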